### Objectives {7}

The I’M WOMAN trial is a randomised, placebo-controlled trial to assess the effects of IM and IV tranexamic acid on PPH, adverse events and other important maternal health outcomes in women at increased risk of PPH. It will:Assess the effect of tranexamic acid on the risk of PPH and other bleeding-related outcomesCompare the effects of IM and IV tranexamic acid on the risk of PPHCompare the effects of IM and IV tranexamic acid on the risk of adverse events

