#### Inclusion criteria

Women thought to be aged 18 years or older admitted to hospital for a vaginal or caesarean birth and who are known to have one or more risk factors for PPH will be potentially eligible. A list of major risk factors is provided in Additional file 8. If accumulating trial data or newly published research suggests that a particular factor is not strongly associated with an increased risk of PPH, we will focus on recruiting women with other/additional risk factors.

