#### Exclusion criteria

The fundamental eligibility criterion is the responsible doctor’s ‘uncertainty’ about whether to use tranexamic acid in a particular woman. Women should not be randomised if the responsible doctor believes that tranexamic acid is clearly indicated (e.g. you have given tranexamic acid within 12 h or plan to give tranexamic acid) or clearly contraindicated (e.g. known allergy to tranexamic acid).

Site eligibility will be assessed by collecting information on the experience and qualifications of the site staff, the number and route of births, and the incidence of PPH.

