#### Secondary outcomes

Specific to caesarean births:Intraoperative blood loss measured by quantifying the amount of blood in sponges and drapes used in surgery and blood loss from suctioning, excluding amniotic fluidSurgery durationIntraoperative whole blood/red cell transfusionPostoperative haemoglobin (Hb) or packed cell volume (PCV) up to the end of the second postoperative day, if known

All births:Postpartum blood loss measured using a calibrated obstetric drape starting immediately after vaginal birth or once the women are shifted to a bed in the observation area after CS surgery, for 1 h, or up to 2 h if bleeding continues after 1 h and the woman remains in bedBlood pressure and heart rate (lowest recorded blood pressure reading and associated heart rate) up to 24 h after birthInterventions for bleeding (uterotonics, non-trial TXA, blood transfusion, surgical and non-surgical interventions) within 24 h of birthNausea, vomiting and dizziness (when the calibrated drape is removed, the woman will be asked about her nausea, vomiting and dizziness during and since the birth) measured using the number of episodes and/or a score from 1 to 10Pain or adverse skin reactions at injection sites (when the calibrated drape is removed, each injection site will be inspected for local reactions and the woman will be asked about pain at her injection sites)Prespecified maternal adverse events up to discharge, death or 42 days postpartum (thromboembolic events, seizure, sepsis, organ dysfunction, coagulopathy)Other maternal adverse events up to discharge, death or 42 days postpartumMaternal mortality up to discharge, death or 42 days postpartum (all-cause, cause-specific, narrative)Length of hospital stayDays in intensive care unit (ICU)/high dependency unit (HDU)Transfer to another hospitalPrespecified neonatal outcomes up to discharge, death or 42 days (breastfeeding, intracranial haemorrhage, pulmonary haemorrhage, bruising, thromboembolic event, seizure, stillbirth/intrapartum death, neonatal death, cause of death, congenital and genetic abnormalities, adverse events)

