### Data collection and management

#### Plans for assessment and collection of outcomes {18a}

The local trial staff will collect consent, baseline, outcome, and adverse event data and send them to the LSHTM CTU Global Health Trials Group by entering them into the online trial database. All staff authorised to collect trial data will be trained in data collection procedures and GCP. The staff will first enter trial data onto paper case report forms (CRF) and then the trial database to allow easier data control. After completing the consent procedure, an entry form will be used to collect baseline data including the woman’s age, gestational age, parity, recent Hb or PCV if known, multiple pregnancy, planned route of birth, previous PPH, hypertensive disease, placental abnormality, antepartum haemorrhage, and any other PPH risk factors. We will also collect the date and time of randomisation and IM injection sites. We will follow up participants until discharge, death, or the end of the postnatal period (42 days), whichever occurs first, and trained staff will record outcome data onto an outcome form.

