### Adverse event reporting and harms {22}

Maternal and neonatal events which occur as a consequence of the CS or vaginal birth, events which commonly occur in this population independent of the trial treatment, events which are present before randomisation, and events which are recorded as study outcomes, do not need to be reported as adverse events. Although congenital and genetic abnormalities cannot be attributed to the trial treatment because it is given minutes before birth, we will record these on the outcome form.

Events recorded on the outcome form up to discharge, death, or day 42 (whichever is sooner) will be presented to the DMC for regular review, and so will not be reported using the adverse events (AE) reporting procedure. For maternal outcomes, this includes PPH, nausea, vomiting, dizziness, vascular occlusive events, seizure, infection, sepsis, organ dysfunction, and pain or adverse skin reaction at the injection site. For neonatal outcomes, this includes stillbirth/intrapartum death, neonatal death, intracranial and pulmonary haemorrhage, bruising, seizure, and vascular occlusive events.

Other medical events that fulfil the AE definition below will be reported up to 42 days after administration of trial treatment. If a woman is discharged before 42 days, outcome events after discharge and up to 42 days that fulfil the AE definition will be reported, including those on the outcome form. At discharge, women will be given an ‘alert card’ identifying them as an I’M WOMAN trial participant and asked to present this card to anyone providing medical care after discharge, up to day 42. The card will have instructions to ensure the AE reporting procedures are followed. A safety reporting overview is provided in Additional file 5.

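### The stillbirth/intrapartum death item mixes fetal deaths before the injection with deaths after it, which pulls the relative risk for that item towards 1

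*Protocol article*

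**What the plan says.** **Outcome.** The neonatal list under Secondary outcomes includes "thromboembolic event, seizure, stillbirth/intrapartum death, neonatal death, cause of death, congenital and genetic abnormalities". Stillbirth and intrapartum death share one entry; neonatal death is a separate entry. The section Adverse event reporting and harms {22} repeats this split and sends these outcome-form events to the Data Monitoring Committee for regular review.

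**Eligibility.** Women may enter if they are "admitted to hospital for a vaginal or caesarean birth and who are known to have one or more risk factors for PPH". Neither the inclusion nor the exclusion criteria mention fetal death. On the risk factors themselves: "A list of major risk factors is provided in Additional file 8".

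**Baseline data.** The items named under Plans for assessment and collection of outcomes {18a} run from age, gestational age and parity to "multiple pregnancy, planned route of birth, previous PPH, hypertensive disease, placental abnormality, antepartum haemorrhage, and any other PPH risk factors". Fetal status is not among them.

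**Timing.** Under Drug administration and dosage schedule, treatment is given at crowning in vaginal births and after draping, before incision, in caesarean births. Under Implementation {16c}, a woman counts as randomised when the first intramuscular injection begins.

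**Attribution.** Section {22} reasons: "Although congenital and genetic abnormalities cannot be attributed to the trial treatment because it is given minutes before birth", and then says these abnormalities will still be recorded on the outcome form. It also takes events present before randomisation out of adverse event reporting. Neither statement is applied to stillbirth as an outcome.

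**The concern.** Only a death after the injection can be caused by it. With treatment this close to birth, a fetus alive at treatment can be stillborn only in a short interval. Deaths before labour, or in labour before crowning or draping, come earlier. Some of the recorded risk factors, such as placental abnormality, antepartum haemorrhage and hypertensive disease, may also go with fetal death before treatment.

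The item can therefore be made up largely of deaths that could not respond to treatment. Relative risk is the stated effect measure (Statistical methods {20a}), and it is the measure that such deaths pull towards 1.

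This matters because the trial doses before birth, whereas the Background says that trials for prevention of postpartum haemorrhage gave treatment after cord clamping, and the drug crosses the placenta. The infant evidence cited under Benefits and harms for maternal dosing before birth is a randomised trial of 120 women. A trial of about 30,000 could add much to that. An analysis plan written later can choose a denominator, but it cannot reliably restore a fetal status that nobody recorded before the injection.

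**Working it through.** **Inputs.** The documents give no rate for stillbirth or neonatal death and no numerical allocation ratio, so there is no stated figure to reproduce. Only the total of about 30,000 comes from the protocol. These are assumptions:

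- *a*: proportion of all births with fetal death before the injection, 0.5% to 3%
- *b*: proportion dying between injection and birth on placebo, 0.1%
- true relative risk for deaths after injection: 2.0
- 20,000 tranexamic acid (both routes) v 10,000 placebo; 24,000 v 6,000 as a variant

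**Formulas.** Placebo risk p0 = a + b; tranexamic acid risk p1 = a + 2b.

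- Apparent RR = (a + 2b)/(a + b)
- SE of log RR = √[(1 − p1)/(n1·p1) + (1 − p0)/(n0·p0)]
- Power = Φ(ln RR/SE − 1.96), two-sided 5%

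**Lower end, a = 0.5%.** p0 = 0.006 and p1 = 0.007, so 60 v 140 expected deaths. RR = 1.167. SE = √(0.993/140 + 0.994/60) = 0.154. Power = Φ(0.154/0.154 − 1.96) = 17%.

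**Upper end, a = 3%.** p0 = 0.031 and p1 = 0.032, so 310 v 640 deaths. RR = 1.032. SE = √(0.968/640 + 0.969/310) = 0.068. Power = Φ(0.0317/0.0681 − 1.96) = 7%.

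**Babies alive at treatment.** About 10 v 40 deaths. RR = 2.0. SE = √(0.998/40 + 0.999/10) = 0.353. Power = Φ(0.693/0.353 − 1.96) = 50%. Taking the 0.5–3% out of the denominators lowers this only to 49–50%. With about 10 placebo deaths the normal approximation is rough.

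| a | b | share of placebo deaths before treatment | apparent RR | power, all births | power, alive at treatment |
|---|---|---|---|---|---|
| 0.5% | 0.1% | 83% | 1.17 | 17% | 50% |
| 1% | 0.1% | 91% | 1.09 | 11% | 50% |
| 2% | 0.1% | 95% | 1.05 | 8% | 49% |
| 3% | 0.1% | 97% | 1.03 | 7% | 49% |
| 0.5% | 0.5% | 50% | 1.50 | 94% | 99% |

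The last row is the mild case: when deaths before and after treatment are equally common, little power is lost. With 24,000 v 6,000, the first four rows give power of 6–13% for all births and 35–36% for babies alive at treatment.

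**What is not diluted.** For events that only a liveborn baby can have, deaths before treatment multiply the risk in both arms by (1 − a), so the relative risk is unchanged. Take 3% dead before treatment, 0.5% of the rest dying during or soon after birth, and a true RR of 2.0:

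- Pooled perinatal death: (0.03 + 0.97 × 0.010)/(0.03 + 0.97 × 0.005) = 1.14; power 54% at 20,000 v 10,000.
- Neonatal death alone: RR 2.0. If half of the 0.5% die after birth, p0 = 0.97 × 0.005 × 0.5 = 0.0024 and power is 86%; if four-fifths do, power is 97%.

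**Risk difference.** p1 − p0 = b in every row, whatever the value of *a*. The earlier deaths add variance but do not bias the difference.

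**The case against.** The strongest reply has four parts.

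1. **Neonatal death is already separate.** A reader might infer that earlier fetal deaths hide every signal of harm in babies alive at treatment. The documents do not support that. Deaths after birth are counted on their own, and if treatment minutes before birth did cause deaths, many would probably fall there. This stands, and it confines the point to one item and to any pooled death endpoint.
2. **The denominator hardly matters elsewhere.** A reader might also infer that seizure, bruising, haemorrhage and breastfeeding are distorted. Their relative risks do not change. This stands.
3. **The forms are not shown.** The article's baseline list is introduced as non-exhaustive and ends with an open category. The entry form, the outcome form, Additional file 8 and the schedule of events in Fig. 2 were not available. Cause of death is collected, and the slash in the item may stand for two tick-boxes. So it cannot be said that fetal status goes unrecorded. This stands and makes the fix conditional. Even so, a cause of death or an antepartum/intrapartum split is not a record of status at the injection, because an intrapartum death can precede crowning or draping.
4. **Denominators belong in the analysis plan.** That is true of the choice of denominator, but not of the data it needs, which must be collected before treatment.

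**Conclusion.** The point holds for the stillbirth/intrapartum death item and for any pooled perinatal death endpoint. As described, the item combines deaths that treatment could not have caused with deaths that it could. No stated criterion or named baseline item separates them, and the protocol applies the corresponding timing argument only to congenital and genetic abnormalities.

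The size depends wholly on assumed rates. If deaths before treatment are 5 to 30 times as common as deaths between treatment and birth, a true doubling looks like a 3–17% increase and power falls from about 50% to 7–17%. If the two are equally common, the loss is a few percentage points. Even restricted, the item has only moderate power at the assumed 0.1%.

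This is a modest, inexpensive improvement to one secondary safety item. It does not show bias between arms, does not touch the primary outcome, and does not mean that the trial could not detect harm to babies.

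**What to change.** First check the entry form. If it does not already hold the item, then:

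- record fetal status (alive, known dead, not known) before the first injection, for each baby in a multiple pregnancy;
- report fetal deaths known before treatment separately, by arm and descriptively only;
- state that stillbirth/intrapartum death, and any pooled perinatal death, are analysed among babies not known to be dead at treatment, and use the same split in reports to the Data Monitoring Committee.

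Because status is fixed before randomisation, the restriction keeps the randomised comparison. Eligibility and treatment do not change, and all women stay in the analysis of postpartum haemorrhage.

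The cost is one form item and one sentence on the denominator. The drawback is that some entries will be "not known". Those babies stay in the analysis, so some dilution remains.

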### Participant timeline {13}

Participant timeline and schedule of events are presented in Figs. 1 and 2.

**Fig. 1 Fig1:**
[figure not shown]
Participant timeline

**Fig. 2 Fig2:**
[figure not shown]
Schedule of events

### Sample size {14}

Two main factors determine the number of patients needed in a trial—the estimated event rate and the size of the treatment effect.

#### Estimated event rate

In trials of tranexamic acid for PPH prevention, the event rate (a clinical diagnosis of PPH) varies from 8 to 15% depending on the mode of delivery [6, 7, 9]. We assumed an event rate of 11.5% in the placebo group, based on a roughly 50:50 ratio of vaginal to caesarean births.

#### Size of the treatment effect

Based on the existing evidence in PPH prevention and surgical trials, we assumed a 25% reduction in PPH with tranexamic acid (RR = 0.75).

A trial of about 30,000 women has almost 90% power to detect that (1) tranexamic acid is more effective than placebo and (2) IM tranexamic acid is at least 60% as effective as IV tranexamic acid. We assumed a two-sided type 1 error rate of 5% for the superiority arm and a one-sided rate of 2.5% for the non-inferiority arm. Our sample size and power calculations were made using methods described by Stucke and Kieser (2012) [32]. We confirmed our results using simulation. An optimal allocation ratio was used to maximise study power with patients allocated to receive IM tranexamic acid, IV tranexamic acid and placebo.

Because the true event rate and treatment effect are unknown, we will re-estimate the sample size if unplanned interim analyses indicate a lower-than-expected event rate or if new information emerges which changes beliefs about the expected treatment effect.

### Recruitment {15}

We will use wall posters and brief information leaflets to inform pregnant women attending antenatal clinics and labour wards about the trial (see Additional file 3). Information may also be provided in videos. To avoid unnecessarily approaching women who will not be suitable, the site investigator will screen the medical records of women attending the hospital to give birth to see if they have a risk factor(s) for PPH and check how old they are or are thought to be. The site investigator will approach eligible women and invite them to take part in the trial and carry out formal screening. This will first involve giving information and seeking consent.

### Assignment of interventions: allocation

#### Sequence generation {16a}

An IT coding expert supported by a statistician will prepare a randomisation list detailing the allocation sequence (the order in which treatment groups are allocated) using a computerised random number generator. A unique randomisation number will be linked with each treatment allocation. We will use blocking to ensure the required allocation ratio is maintained throughout the trial.

#### Concealment mechanism {16b}

The IT expert will send the randomisation list to the clinical trial supplies company so that blinded treatment packs can be prepared. The company will produce, label and package tranexamic acid and placebo ampoules into patient treatment packs as per the randomisation list. Tranexamic acid and placebo ampoules will look identical. The trial staff (coordinating centres and sites) will not have access to the randomisation list until after the final database lock.

#### Implementation {16c}

Once a woman is confirmed to be eligible, just prior to skin incision in caesarean section births (after draping), or at crowning in vaginal births, a treatment pack will be taken from a box of packs by a delegated member of the research team. The woman is considered to have been randomised once administration of the first IM injection has started. Each site will keep a log of women they enrol in the trial.

### Assignment of interventions: blinding

#### Who will be blinded {17a}

Trial participants, trial staff, healthcare providers, outcome assessors and data analysts will be blinded. The trial treatment packs will look identical except for the unique randomisation number. All women will receive two IM injections and one IV injection to ensure blinding of the route of tranexamic acid administration. The IM and IV treatment kits within each treatment pack will be clearly labelled to show the intended route of administration.

#### Procedure for unblinding if needed {17b}

There should be no need to unblind the allocated treatment. If a woman develops PPH, she should receive all clinically indicated treatments, which can include tranexamic acid. Because a second 1-g dose of tranexamic acid is well within the usual dosing range, it is not necessary to find out whether a particular woman received tranexamic acid or placebo as part of the I’M WOMAN trial. Even if a particular woman has received tranexamic acid within the trial, a second 1-g dose of tranexamic acid can safely be given. Nevertheless, if the clinician believes that a woman’s care depends importantly upon knowledge of whether the participant received tranexamic acid or placebo, it is possible to unblind. If urgent unblinding is necessary, the CTU will provide an emergency 24-h telephone service. The caller will receive a voice message, text message or email informing them whether the woman received tranexamic acid or placebo. The investigator should complete an unblinding request/report form within five working days of unblinding. If a suspected unexpected serious adverse reaction (SUSAR) is reported, unblinding may be needed for reporting to regulatory agencies and ethics committees.

### Data collection and management

#### Plans for assessment and collection of outcomes {18a}

The local trial staff will collect consent, baseline, outcome, and adverse event data and send them to the LSHTM CTU Global Health Trials Group by entering them into the online trial database. All staff authorised to collect trial data will be trained in data collection procedures and GCP. The staff will first enter trial data onto paper case report forms (CRF) and then the trial database to allow easier data control. After completing the consent procedure, an entry form will be used to collect baseline data including the woman’s age, gestational age, parity, recent Hb or PCV if known, multiple pregnancy, planned route of birth, previous PPH, hypertensive disease, placental abnormality, antepartum haemorrhage, and any other PPH risk factors. We will also collect the date and time of randomisation and IM injection sites. We will follow up participants until discharge, death, or the end of the postnatal period (42 days), whichever occurs first, and trained staff will record outcome data onto an outcome form.

#### Plans to promote participant retention and complete follow-up {18b}

Follow-up will take place in a hospital and should be minimal, so there is no need for strategies to increase retention. A woman can withdraw from the trial at any time. She may give her reason for withdrawal but she does not have to. If a woman withdraws from the trial, we will analyse data collected to the point of withdrawal, but no other data will be collected unless the woman gives permission. In all cases, we will respect the woman’s wishes. At discharge, women will be given an ‘alert card’ identifying them as an I’M WOMAN trial participant and asked to present this card to anyone providing medical care after discharge, up to day 42. The card will have instructions to ensure the AE reporting procedures are followed.

#### Data processing pathway {19}

Data will be collected at each site by local investigators and sent to the LSHTM CTU Global Health Trials Group. On completion of the paper CRF, data will be submitted by authorised investigators into the trial database held by the LSHTM CTU Global Health Trials Group, accessed via a unique username, password, and PIN. Data will have a one-pass data entry by investigators entering forms directly onto the trial database. One hundred per cent of data received will be subject to automatic electronic validation checks built into the database, such as checks of ranges and illogical values, and manual review, in line with the I’M WOMAN Database Development and Validation Plan and I’M WOMAN Data Management Plan. Missing data will be recorded and presented as such, not imputed. Correction of discordant data will be resolved through queries on the trial database via the inbuilt query management system, followed up regularly until resolved.

